**Fig. 3 Fig3:**
[figure not shown]
CONSORT flow chart of projected study enrollment

Therapists enrolled in the study retain the right to withdraw consent at any time. The protocol will be discontinued at any site where procedures become burdensome or otherwise impinge on the routine performance of participating staff. Analysis of intervention impacts and potential harm will be continuous throughout the trial. In cooperation with the administration of partnering sites, investigators will provide full study debriefing and offer counseling referrals to any participant aggrieved or injured due to trial participation.

### Study measures

*The Inventory of Therapy Techniques for Adolescent Behavior Problems* (ITT-ABP) is a post-session therapist-reported fidelity tool that meets key criteria for pragmatic measures: relevance to stakeholders, low burden, broad applicability, strong psychometrics, and usefulness for data-driven decision-making (i.e., it is actionable). It requires 1–2 min to complete and was derived from validated observational fidelity tools for manualized treatments via a stakeholder-informed instrument adaptation process. The 13 FT and 15 CBT items each measure the extensiveness (i.e., thoroughness and frequency) with which each technique was used on a 5-point Likert-type scale: 0 = Not at all, 1 = A little bit, 2 = Moderately, 3 = Quite a bit, 4 = Extensively. Germane to rigor, ITT-ABP items derive from a validated observational EBT fidelity tool for manualized treatments that has shown strong construct and predictive validity in studies of treatment fidelity and fidelity-outcome links [14] with youth samples including conduct-disordered, depressed, and substance-using teens. The FT scale [28] and CBT scale ([name], et al., Core elements of CBT for adolescent conduct and substance use problems: developmental psychopathology, clinical techniques, and case examples; submitted) were each enhanced via a comprehensive distillation process to identify the respective core treatment techniques of each approach as evidenced in controlled research with manualized treatment models for AEPs. Study therapists will complete the FT items, CBT items, or both, depending on which EBT(s) they elect to train. Baseline covariates will be assessed via three therapist-reported measures.

The *Organizational Social Context measure* [29] yields scaled scores that can be compared to national norms describing the organizational context of behavioral health clinics with regard to organizational culture, organizational climate, and work attitudes. The *Evidence-Based Practice Attitude Scale* [30] is a 15-item measure of clinician attitudes regarding appeal of EBTs, required use of EBTs, openness to trying EBTs, and unfavorable attitudes toward EBTs. The *Therapist Self-Reported EBT Proficiency* measure [31] averages therapists’ own judgments about their degree of allegiance to, and their perceived technical skill in, FT and CBT.

### Study interventions: MTFS-I components

MTFS-I intervention components are designed to be implemented flexibly in behavioral care settings, and therefore participating therapists are permitted to engage in concurrent training, supervision, and consultation.

#### MTFS-I training component

Online MTFS-I training will be used to increase validity in self-reporting on EBT fidelity and also to model high-fidelity EBT delivery. Online training has proven comparable or superior to in-person workshops in increasing clinical knowledge, self-reported use of treatment skills, and clinical proficiency [22, 32]. Front-line clinicians report comfort with online training, believe it to be efficacious [33], and believe it increases training accessibility and engagement [22]. MTFS-I training will be delivered weekly in two connected parts. (1) Self-monitored learning modules are brief descriptions and related clinical exemplars describing FT and CBT items from the ITT-ABP. Each learning module covers 2–3 items. Self-monitored training can reduce self-report biases of various kinds by providing continuous training in unbiased, accurate reporting [34]. (2) Mock session coding consists of 5–8 min video segments modeling examples of FT and CBT techniques on the ITT-ABP, illustrating a range from low to high extensiveness in order to support differentiated scoring. Trainees code segments directly after completing a corresponding self-monitored training module for those items in order to reinforce training elements. Trainees then submit ITT-ABP ratings for the given video segment and immediately view gold-standard scores, along with justification for the gold-standard scoring.

As discussed previously, these procedures mimic well-established observational training methods and leverage immediate corrective feedback on objectively rated samples of desired performance [25]. In addition to supporting self-report reliability and accuracy, these methods have strong potential for increasing EBT use via observational learning mechanisms prompted by modeling of quality EBT delivery. Although live coaching and guided skills practice are the most effective means to acquire new clinical skills [32], video-based modeling has also shown promise for increased EBT delivery (see, e.g., [35]).

#### MTFS-I feedback component

MTFS-I also features monthly feedback reports that summarize cumulative EBT use for each active case, based on therapist-reported ITT-ABP data. Feedback reports can contain (1) mean values for each EBT item and for the average EBT scale(s) (FT and/or CBT) aggregated at the client, therapist, and/or site levels; (2) aggregated EBT scale means plotted against benchmark fidelity levels. Figure 4 depicts content from a sample feedback report. A key predictor of adoption of innovative technology is fit between the technology and service context [36]. To promote compatibility and clinical relevance and increase collaborative investment in MTFS-I, after a lead-in period in which all sites gain familiarity with a basic report template, each site will define its own benchmark levels for EBT fidelity [23] to be specified in feedback reports, along with benchmarks drawn from research studies of FT and CBT models, respectively. Reports spur direct comparison between therapist self-reports of EBT delivery versus agency-specified benchmarks, precipitating data-driven self-correction that motivates movement toward fidelity goals. Data-based case feedback along multiple dimensions, including fidelity, is also thought to optimize change potential [23]. Each site will confer on the optimal design of feedback reports, user-friendly infographics of ITT-ABP data, the pragmatics of routine MTFS-I use, and potential organizational and staff-related facilitators and barriers to report use [37]. Feedback reports delivered to therapists will contain therapist-level data, whereas supervisor reports will contain agency-aggregated data, preserving therapist autonomy to share their own data in supervision.

**Fig. 4 Fig4:**
[figure not shown]
Sample of monthly feedback report based on ITT-ABP data

### Study interventions: MTFS-I consultation

In keeping with evidence-informed guidelines for effective clinical facilitation (see [26]), MTFS-I consultation will focus on four interrelated strategies: discussion about recently viewed video vignette(s) (invoking retrieval practice and microlearning mechanisms), review of recently distributed feedback reports (cognitive rehearsal with increasing challenge), review of therapist-prepared case summaries combined with action planning for upcoming sessions (behavioral and cognitive rehearsal with variability), and live review of segments from submitted audiotapes (behavioral rehearsal with increasing challenge). Review of feedback reports will capitalize on data-driven decision-making, which has been shown to increase performance and productivity across a range of industry, education, and clinical service settings [38]. Sites will select the consultation format that fits best with extant site supervision practices: weekly 20–30 min by phone, bi-weekly 40–60 min by phone, or monthly 90–120 min in person. Although clinical consultation of this kind requires substantial resource commitments and extramural support, it is a common strategy shown to be feasible and valuable for scaling behavioral innovations across a variety of behavioral care systems, and community clinicians feel meaningfully supported by expert consultation [39]. Moreover, expert consultation on feedback reports has been shown to increase uptake of outcomes-focused MBC [13]. All study therapists will also receive routine technical assistance on MTFS-I system navigation and EBT data submission throughout the Implementation phase.

### Study procedures

All study data, including clinician demographics, self-reported fidelity checklists, and session audiotapes, will be obtained using data-secure procedures (e.g., ShareFile).

#### EBT fidelity and MTFS-I uptake data collection

ITT-ABP checklists and session audio recordings will be collected at all sites during the Baseline and Implementation phases. During the Implementation phase, therapists and supervisors will complete online MTFS-I training activities (self-monitored learning modules, mock vignette coding). To assess between-condition differences in consultation activities, therapists in both conditions will report on the extent to which training materials and feedback reports are discussed during clinical supervision.

#### Observational coding of EBT delivery

Session audio recording is a minimally intrusive procedure widely accepted by families and therapists in our previous studies that has proven feasible in usual care for youth behavioral health [19]. We will randomly select one recorded session from the Early phase (sessions 1–3) and the Later phase (sessions 4+) of treatment for each client to code with the observer version of the ITT-ABP [21]. Projecting 192 clients yielding 1.5 selected recordings apiece (factoring in treatment dropout after the Early phase sessions), we anticipate coding *n* ~ 288 recordings, of which 20% will be double-coded to establish observer reliability.

### Power analysis

Power to detect an experimental effect is based on *n* = 288 audiotaped sessions coded. The study is optimally powered (exceeding .80) to detect a between-condition effect size of *d* = .30 (small) or greater when data are combined across sites. Power calculations were conducted using Optimal Design 3.01 [40]. With nested designs, power is substantially affected by number of sites as well as clusters (therapists and clients) within site [41], and less so by cases (sessions) within cluster. Aggregating across site, and assuming 32 therapists (*unit of randomization*) treating 6 clients each and submitting 1.5 taped sessions for review (*unit of analysis*) and moderately sized within-cluster intraclass correlation coefficients (ICCs) (*ρ* = .05) [42], yields optimal levels of power (exceeding .80) for even small effects (*d* = .30) and increasing power (exceeding .90) with effect sizes of *d* = .40 and greater. Previous research has yielded effect sizes *d* = .40–.50 using a similar design [43].

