## Methods/design

### Trial design

The trial design is a two-group randomized trial with baseline comparison: Following a 4-month Baseline phase, therapists working in behavioral health treatment sites will be randomized across two experimental conditions, Training Only versus Training + Feedback + Consultation, for a 1-year Implementation phase. During both study phases we will collect EBT fidelity data (therapist-reported checklists, session audiotapes); during the Implementation phase we will also collect MTFS-I uptake data (training and consultation activity). In Aim 1, by comparing Baseline versus Implementation data, we can examine the effectiveness of the MTFS-I training component for enhancing EBT fidelity across study sites, yielding proof-of-concept data in accord with the well-established Stage Model of behavioral treatment development [27]. In Aim 2, by experimentally comparing Training Only versus Training + Feedback + Consultation, we can test the added value of MBC procedures combined with expert consultation procedures [26] for enhancing MTFS-I benefits. Also the quasi-experimental analysis of Baseline data (averaged across all study therapists) versus Training Only condition data will shed light on the unique effects of the online training component, which is the most pragmatic feature of the overall MTFS-I package. Comparing averaged Baseline-phase data versus the Training + Feedback + Consultation condition will also provide insight on the full MTFS-I effects. It was not possible to include a no-intervention or waitlist control group because sites unilaterally preferred that all study therapists receive a clinically meaningful training experience. To maximize clinical utility and trainee motivation, each study therapist will select whether they want to train in FT, CBT, or both; training in both approaches will double the time commitment (to approximately 40 total min per week) for the given trainee. Figure 2 is the Standard Protocol Items: Recommendations for Interventional Trials (SPIRIT) diagram depicting the schedule of trial enrollment, interventions, and assessments. Additional file 3 presents the SPIRIT checklist. Study sites and eligibility, sample size, randomization, and contamination procedures.

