**Fig. 2 Fig2:**
[figure not shown]
SPIRIT diagram depicting the schedule of trial enrollment, interventions, and assessments

To host trial activities we will recruit four behavioral health outpatient clinics that attest to endorsing FT and CBT as staples of their clinical practice. All full-time clinicians will be eligible to participate. We project to enroll 32 therapists total (8 therapists per site [6 active slots plus 2 to replace dropouts]) treating 192 cases (24 therapist slots × 8 consenting cases/year). Treatment will average ~ 6 sessions/case (given routine therapy attrition), yielding ~ 1152 post-session therapist-reported checklists, about half with accompanying recordings (*n* ~ 576); half of these (~ 288 sessions) will be coded for EBT fidelity by research staff. Figure 3 shows a Consolidated Standards of Reporting Trials (CONSORT) flow chart of projected study enrollment. We will randomize volunteer therapists within each site to study condition at the start of the Implementation phase, given that MTFS-I procedures target individual therapists and their supervisors rather than entire agencies [24]. We will not randomize supervisors to condition, for two reasons. Because therapists in the Training Only condition will engage in solitary online training activities and will not review feedback reports or participate in expert consultation meetings with supervisors, we do not anticipate substantial supervisor “crossover” effects should a given supervisor oversee therapists in both conditions. Also, many clinics have only one supervisor, making it neither practical nor ecologically valid to randomize supervisors into condition. To guard against experimental contamination, supervisors will be asked not to review feedback reports in the presence of Training Only therapists.

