### Trial status

This clinical trial (registration ClinicalTrials.gov NCT03722654; original protocol, October 29, 2018) has not yet enrolled participants. We anticipate enrolling initial participants in November 2019 and completing recruitment in November 2020.

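### The between-condition power uses all 288 projected coded sessions without saying whether they include pre-randomization Baseline tapes, and the stated power is not reached on either reading

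*Protocol article*

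**What the plan says.** The sample-size paragraph after Figure 2 projects 32 therapists "treating 192 cases (24 therapist slots × 8 consenting cases/year"), then about 1152 checklists, about 576 recordings and about 288 coded sessions. The section on observational coding reaches the same number by another route: "Projecting 192 clients yielding 1.5 selected recordings apiece", hence about 288 recordings to code. Neither place assigns these totals to a phase.

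The collection period has two phases. Under Trial design: "Following a 4-month Baseline phase, therapists working in behavioral health treatment sites will be randomized across two experimental conditions", followed by a one-year Implementation phase. Under data collection: "ITT-ABP checklists and session audio recordings will be collected at all sites during the Baseline and Implementation phases". The sample-size paragraph also puts randomization at the start of Implementation.

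The Power analysis section takes as its basis "288 audiotaped sessions coded. The study is optimally powered (exceeding .80) to detect a between-condition effect size of" d = .30 or more. It describes its sample as 32 therapists "treating 6 clients each and submitting 1.5 taped sessions for review", with ICC .05. It says that this "yields optimal levels of power (exceeding .80) for even small effects" (d = .30), and that power exceeds .90 from d = .40 upward. The effect in question is the between-condition one.

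**The concern.** One number does two jobs. In the sample-size and coding sections, 288 is everything the trial expects to code. In the power section, it is the sample for a contrast that exists only after randomization. Both can be true only if no Baseline tape is coded. Aim 1 rules that out: it compares Baseline with Implementation on therapist reliability and accuracy, which are defined against observer scores, and on observer-coded technique use.

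The time base points to the same gap. The 192 cases come from an annual rate, while collection runs for 4 + 12 = 16 months.

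Aim 2 is the only randomized comparison. A reader of the power section would take it as well powered for a small effect, on a sample that may include sessions recorded before the conditions existed.

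**Working it through.** **Counts (all reproduce)**
- Cases: 24 slots × 8 per year = 192; also 32 therapists × 6 clients = 192.
- Checklists: 192 × 6 = 1152. Half recorded = 576; half of those coded = 288.
- Coded tapes: 192 × 1.5 = 288; also 32 × 6 × 1.5 = 288, or 9 per therapist.

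The power sample is therefore the whole projected yield.

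**Power inputs**
- From the Power analysis section: J = 32 therapists as the unit of randomization, ρ = .05, d = .30 and .40.
- Assumed, because the article does not give them: two-sided α = .05 and 16 therapists per arm. The Data analysis plan says that alpha will be adjusted for multiple contrasts; any such adjustment lowers the figures below.

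**Formula.** With m tapes per therapist, the standardized difference has SE² = 4[ρ + (1 − ρ)/m]/J. Power is taken from the noncentral t distribution with J − 2 = 30 df. Normal-approximation values are in parentheses.

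**Reading 1: all 288 tapes are from Implementation (m = 9)**
- SE² = 4(.05 + .95/9)/32 = .01944; SE = .1394.
- d = .30: .30/.1394 = 2.15, power .549 (.576).
- d = .40: .40/.1394 = 2.87, power .793 (.818).
- Smallest d with 80% power: about .39 (normal).

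**Reading 2: 288 covers both phases.** The article gives no split, so these are illustrations.
- *Even accrual over 16 months:* 288 × 12/16 = 216 Implementation tapes, m = 6.75. SE² = 4(.05 + .95/6.75)/32 = .02384; SE = .1544. Power .468 (.493) at d = .30 and .708 (.736) at d = .40. Smallest d with 80% power: about .43.
- *Baseline takes 4/12:* 192 tapes remain, m = 6, SE = .1614. Power .436 (.460) and .670 (.698).

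| Implementation tapes | Power, d = .30 | Power, d = .40 |
|---|---|---|
| Stated in article | > .80 | > .90 |
| 288 | .55 | .79 |
| 216 (illustration) | .47 | .71 |
| 192 (illustration) | .44 | .67 |

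**Separating the two effects at d = .30.** From .80 to .549 is a gap of about .25 that exists with every tape in Implementation. From .549 to .468 is a further .08 from the phase split.

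**Sensitivity with 288 tapes**
- No clustering, two-sided: .721 at d = .30 and .924 at d = .40.
- Site blocking that removes all therapist variance: .743 and .936 (normal).
- ρ = .01: .688 and .904 (normal).
- One-sided with no clustering: .816 at d = .30. One-sided with clients as clusters: .81.

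So the d = .40 claim can be met if therapist clustering is removed or nearly so. The d = .30 claim needs a one-sided test that also ignores therapist clustering. With 216 tapes and no clustering at all, two-sided power is .597 and .836.

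**If 288 is Implementation only.** At the stated annual rate, 4 months of Baseline would add 24 × 8 × 4/12 = 64 cases and 64 × 1.5 = 96 coded tapes, for totals of 256 and 384. This assumes even accrual and no client spanning both phases.

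**The case against.** The strongest reply is that 8 cases per year and a one-year Implementation phase match, so 192 and 288 describe the Implementation year and the power sample is right. That reading is possible. The Condition sample would then stand, and the defect would move to the totals, which leave out Baseline. The Data analysis plan calls the Aim 1 contrasts exploratory, so that omission would not touch the randomized test. The stated power would still not be reached.

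The projected enrolment flow chart (Figure 3) is not visible here and may give counts by phase. If it divides the 192 cases, 288 is too many for the Condition test; if it adds Baseline cases, the totals in the text are incomplete. Either way a sentence needs correcting.

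Baseline tapes could sharpen the Condition contrast as a covariate. They add no post-randomization sessions, however, and the power section claims no such gain.

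Three stronger conclusions that a reader might infer are not supported:
- *The phase split causes the power shortfall.* Most of the shortfall is there with all 288 tapes in Implementation.
- *Baseline coding would use up a fixed allowance of 288 tapes, so a quota by phase is needed.* The coding section selects one early and one later session for each client and then projects about 288. That is an expectation and not a cap, so coding Baseline clients takes nothing from Implementation clients.
- *216, 192, 256 or 384 are the correct figures.* All rest on assumed accrual. The 192-tape case is the weakest: it reads the window in Trial status, "We anticipate enrolling initial participants in November 2019 and completing recruitment in November 2020", as client accrual, although the article does not say whether those participants are therapists or clients.

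**Conclusion.** The point holds as an inconsistency in the planning figures plus a power statement that does not reproduce. The article does not say which phase or phases the 192 cases and 288 tapes cover. One of two things follows: the between-condition sample is overstated, or Baseline is left out of the totals.

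With the article's 32 therapists and ICC of .05, and with two-sided .05 and equal arms assumed, power at d = .30 and .40 is about .55 and .79 at best. It is about .47 and .71 if a quarter of the tapes are Baseline. Neither reading gives the stated values of above .80 and above .90. The ambiguity over phase is worth about .08 at d = .30 under even accrual. Resolving it would not restore the claim, because about .25 of the gap is unrelated to phase.

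**What to change.** - State whether the 192 cases and 288 coded tapes refer to Implementation only or to both phases, and give projected cases and coded tapes for each phase in the sample-size and coding sections.
- Restate the between-condition power, or the smallest detectable d, on Implementation tapes only, with therapist as the cluster and with alpha and sidedness given. On the present inputs the detectable d at 80% power is about .39 with 288 tapes, or about .43 in the 216-tape illustration. The sponsor should replace these with values from its own accrual projection.

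The cost is a few sentences of revised text and a less favourable stated power. The conduct of the trial and the session-selection rule need not change. Trial status says that no participant has yet been enrolled, so the correction can be made before any data exist.

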### Data analysis plan

Study data will have a three-level nested structure: clients within therapists within sites (we will average across sessions for each client). The basic analytic approach for these nested data will be multilevel mixed effects models examining the effects of Phase (Baseline versus Implementation) and Condition (Training Only versus Training + Feedback + Consultation) on dependent variables aggregated across each time period: 4-month Baseline phase (prior to MTFS-I training) and 12-month Implementation phase. We will use maximum likelihood estimation for continuous variables and robust weighted least squares for categorical variables. We will model Site and Therapist as random effects in all models. We will include Therapist (age, sex, race/ethnicity, experience, EBT attitudes, EBT proficiency) and Client (age, sex, race/ethnicity) factors at their respective levels to examine potential effects. Effect sizes will be calculated using the standardized *d* effect size indicator, interpreted as the standardized difference between contrasts for Phase and Condition comparisons [41]. Aim 1 exploratory contrasts will examine the Phase (within-subjects) effect, contrasting Baseline versus Implementation across all sites in EBT self-monitoring (reliability, accuracy) and EBT technique use (averaging across FT and CBT techniques). Aim 2 will experimentally test the Condition (between-subjects) effect on MTFS-I uptake, EBT self-monitoring, and EBT technique use.

To analyze EBT self-monitoring, reliability between therapists and observers on FT and CBT technique use will be calculated using the ICC_2,2_ [44]. Conditions will be compared on the relative magnitude of ICCs for each EBT scale. To compare conditions on therapist accuracy, we will use statistical equivalence testing methods, applying the confidence interval approach [45] to examine whether therapist scores are equivalent to corresponding observer scores. To analyze EBT technique use, a series of multilevel mixed effects models will be conducted with a dummy-coded Condition variable included at the Therapist level to test the contrast of main interest; alpha will be adjusted to account for multiple contrasts. For the Aim 1 analyses of Phase contrasts, a product interaction terms will be included to examine Phase by Condition effects; for significant interactions, we will test simple effects by examining Phase contrasts separately within condition.

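### The stated power (above .80 at d = .30, above .90 at d = .40) does not follow from the stated inputs, which give about .55 and .79 at two-sided .05

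*Protocol article*

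**What the plan says.** The power analysis section of the protocol article works from the coded recordings: "Power to detect an experimental effect is based on *n* = 288 audiotaped sessions coded". It then claims: "The study is optimally powered (exceeding .80) to detect a between-condition effect size of *d* = .30 (small) or greater". It sets the structure out as "assuming 32 therapists (*unit of randomization*) treating 6 clients each and submitting 1.5 taped sessions for review (*unit of analysis", and the clustering as "moderately sized within-cluster intraclass correlation coefficients (ICCs) (*ρ* = .05". It says that this "yields optimal levels of power (exceeding .80) for even small effects (*d* = .30", with "increasing power (exceeding .90) with effect sizes of *d* = .40 and greater". The calculation is attributed to Optimal Design 3.01. The section also cites effects of d = .40 to .50 from earlier research with a similar design.

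The section gives no alpha, no sidedness, no covariate R-squared and no gain from blocking on site. The data analysis plan section adds that "alpha will be adjusted to account for multiple contrasts", without a number of contrasts. The trial design section allows for 24 active therapist slots, with the other 8 of the 32 therapists as replacements for dropouts.

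**The concern.** The article prints the inputs of a standard two-arm cluster-randomized calculation together with its outputs, so the outputs can be checked. For d = .30 a quick check already fails. A simple two-sample comparison at two-sided .05 needs roughly 350 independent observations for 80% power, and the plan has 288 clustered ones.

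The Condition contrast (Aim 2) is the trial's only randomized comparison. Readers who take the power section at its word may read a null result there as evidence against a small effect. If true power at d = .30 is near one half, a null result says little about effects of that size.

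**Working it through.** **Inputs from the power analysis section**
- Therapists randomized: J = 32. An equal split of 16 per arm is assumed; the ratio is not given, and equal is the most favourable.
- Sessions per therapist: m = 6 × 1.5 = 9, and 32 × 9 = 288, which matches the stated total.
- Intraclass correlation: ρ = .05.
- Assumed, because not stated: two-sided alpha of .05.

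**Formula** (standardized effect, treatment assigned at cluster level)
- Var = 4[ρ + (1 − ρ)/m]/J = 4[.05 + .95/9]/32 = .01944, so SE = .1394.
- Equivalently, the design effect is 1 + 8 × .05 = 1.40 and the effective sample is 288/1.40 = 205.7 sessions.
- Noncentrality λ = d/SE, referred to the noncentral t with J − 2 = 30 df (critical value 2.042).

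**Result on the stated inputs**
- d = .30: λ = 2.151, power .549 (stated: above .80).
- d = .40: λ = 2.869, power .793 (stated: above .90).
- d = .50: λ = 3.586, power .934.
- Detectable d: .404 for 80% power, .467 for 90%.
- For .80 at d = .30 with 9 sessions each, 56 therapists give .798 and 58 give .812, so about 58 would be needed.

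The plan's own figures are not reproduced. I then looked for a reading that would reproduce them.

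| Reading (two-sided .05 unless noted) | d = .30 | d = .40 |
|---|---|---|
| Stated inputs, noncentral t | .549 | .793 |
| Same, normal approximation | .576 | .818 |
| One-sided .05, ρ = .05 | .676 | .877 |
| Site blocking, 27 df, no variance removed | .546 | .790 |
| Half the between-therapist variance removed | .620 | .855 |
| All between-therapist variance removed | .712 | .919 |
| Three levels, therapist and client ICC .05 each | .541 | .786 |
| Client means as the unit, 6 per therapist | .436 | .670 |
| Clients as clusters, therapists ignored | .706 | .916 |
| 288 independent sessions | .718 | .923 |
| 288 independent sessions, one-sided | .815 | .959 |

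Of these rows, only the last meets both stated figures. It needs a one-sided test and no therapist clustering, which contradicts the stated ρ of .05. Ignoring clustering, or removing all between-therapist variance, meets the d = .40 claim but not the d = .30 claim.

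**Sensitivity, not needed for the conclusion**
- 24 therapists with 12 sessions each (24 × 12 = 288): .498 and .741.
- Alpha of .025, as an illustration of the planned adjustment: .429 and .694.
- Therapist ICC of .10 or .20 (assumption): .45 or .33 at d = .30, with 80% detectable d of .46 or .55.

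**The case against.** The strongest reply is that a condensed article may omit inputs. Alpha and sidedness are not given, and the models include therapist and client covariates that could reduce residual variance. Some combinations do reach the stated figures:
- Removing all between-therapist variance and 20% of the within-therapist variance gives .807 two-sided at d = .30.
- A one-sided test with 30% of the variance explained at both levels gives .807 and .956.
- For d = .40 alone, 30% explained at both levels gives .913 two-sided.

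These are optimistic inputs, and the power section states none of them. It attributes the power to the listed inputs. The data analysis plan brings covariates in to examine their effects, and claims no gain in precision from them. In a two-sided test with equal proportions explained at both levels, about 45% would be needed for .80 at d = .30. So the reply shows how the figures could have arisen, not that they are right.

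Four points do stand:
- The .55 and .79 must be given with their two-sided .05 basis.
- The d = .40 shortfall is the milder one. Over the cited range of .40 to .50, power runs from about .79 to .93, so the trial is close to or above conventional power for the effect it expects.
- Since no alpha is printed, one cannot say whether the planned adjustment was built in.
- The 24-slot case pools different therapists who fill one slot, and the adjusted-alpha case uses an illustrative level. Both are useful but optional.

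**Conclusion.** The point holds. On the printed inputs, power is about .55 rather than above .80 at d = .30, and about .79 rather than above .90 at d = .40. This assumes equal allocation, two-sided .05, and no variance explained by covariates or blocking.

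The finding does not depend on the unstated alpha convention, since one-sided .05 with the stated intraclass correlation also misses both figures. At d = .30 the two-sided shortfall remains even if clustering is ignored. Only variance reductions that the section does not mention would close it. The design is adequate for effects of about d = .40 and larger, but not for the small effect the text claims. This should be corrected before the power statement is relied on.

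**What to change.** Restate the power paragraph along these lines: with 32 therapists randomized equally, 9 coded sessions each (288 in total), an intraclass correlation of .05 and a two-sided alpha of .05, power is about .55 at d = .30, .79 at d = .40 and .93 at d = .50; the minimum detectable effect is about d = .40 for 80% power and .47 for 90%. Delete both statements that the study is adequately powered for small effects.

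If the original calculation used a one-sided test, a covariate R-squared or a blocking gain, state that input, justify it, and show power with and without it. Rows for 24 therapists and for the adjusted alpha would be helpful additions once the number of contrasts is fixed.

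The cost is wording in the power section. No therapists or recordings are added; the stated power becomes less favourable.
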